## 5.12 - Dosage escalation plan

The starting dose of carboplatin will be 2 µg. The carboplatin dose will be escalated in cohorts of 3 (maximum of 6 patients in each dose level if DLT occurs). Three patients will be entered first at Dose Level 1. In the absence of DLT, 3 more patients will be entered at the next higher dose level. If 1of 3 patients had DLT, an additional 3 patients will be entered at that dose level. Dose escalation will continue until DLT occurs in at least 2 out of 6 patients. The MTD will be defined as the highest dose level at which at least 5/6 patients could be treated without DLT. If 2 of 3 patients in Dose Level 1 demonstrate DLT, the next cohort of patients will receive Dose Level 0. At least 28 days must elapse between completing enrollment in a cohort level and beginning treatment at the next cohort level.

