# 5 - Treatment Plan

5.1 - Study Design:

Phase I dose escalation study

5.2 - Proposed trial:

Carboplatin in a volume of 54 ml will be administered intracerebrally by convection enhanced delivery at a flow rate of 0.75 ml/hr over 72 hr. The first patient will receive an initial starting dose of 2 µg over 72 hrs (0.667 µg/24 hr). This first patient will be observed for 28 days after completion of the infusion, prior to enrollment of additional patients. In the absence of dose-limiting toxicity (DLT), 3 more patients will be entered at the next higher dose level, which will be double the prior dose (i.e., 4 µg over 72 hrs). If 1of 3 patients exhibits DLT, an additional 3 patients will be entered at that dose level. Dose escalation will continue until DLT occurs in at least 2 out of 6 patients. The maximum tolerated does (MTD) will be defined as the highest dose level at which 3/3 or 5/6 patients could be treated without DLT. Dosage escalation will proceed in subsequent cohorts of 8 µg, 16 µg, 32 µg, 64 µg, 85 µg, 107 µg and 128 µg. If the MTD has not been reached, we will submit a request to the FDA with a schedule for continued escalation until DLT is reached. If 2 of 3 patients demonstrate DLT at 2 µg, the dose will be reduced to 1 µg for the next three patients. DLTs are defined, in the presence of supportive care, as any Grade 3 or 4 toxicity that is possibly, probably, or definitely related to the study drug. The maximum tolerated dosage is defined as the dose level below that causing DLT in at least two patients. The length of the DLT window will be at least 28 days, and this time interval must elapse before completion of one cohort and initiation of the next.

5.3 - Population:

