A CT will be obtained a maximum of 12 hours before the start of the infusion to confirm catheter position. Infusions will start preferably on postoperative day 1, but could be delayed up to postoperative day 7, based on patient’s condition. If the patient’s condition does not allow for infusion, the catheters will be removed. Once catheter placement has been confirmed, patients will undergo infusion of carboplatin. Carboplatin will be infused at a rate of 0.75 mL per hour over 72 hours via a syringe pump. The total flow rate (0.75 ml/hr will be divided among the catheters placed. The catheters and syringe pumps will be attached to a bedside programmable syringe-type microinfusion pump (Medex/Medfusion 3500 Syringe pump or equivalent, which are immediately available for use) via infusion tubing (Vygon Neuro Infusor Infusion catheter system).

The infusion pump will be monitored by the surgical team, including attending neurosurgeons, resident house staff and nurse practitioners. Decisions regarding initiation of infusion and determining if there are problems with the infusion will be the responsibility of the surgical team and supervised by one of the neurosurgical attending physicians ([name]). The infusate will be prepared and supplied by The OSUMC / James Pharmacy Investigational Drug Service (see section 3) at the dose as determined by the dosing schedule (see page 18, section entitled ‘dosing paradigm’) and will be changed every 24 hours by the surgical team. A syringe-type microinfusion pump (see paragraph above) will control the rate of carboplatin infusion into the infusion catheter. The syringe will connect to the infusion catheters via infusion tubing. The infusion rate will be 0.75 ml/hr. Nursing staff will record that the infusion is running, but will otherwise have no responsibilities regarding the infusion pump. For any problems with the infusion or if the infusion pump alarms, the nurses will notify the neurosurgical team. During infusion, vital signs and neurologic status will be assessed and recorded at least every 4 hours. A specific person designated for monitoring the infusion pump and this person’s contact information will be clearly identified in the chart and provided to the patient’s nurse. This person will be a member of the neurosurgical team and will be [name], [name] or [name] or a physician or nurse directly supervised by [name], [name] or [name].

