## 5.13 - Dose-Limiting Toxicity (DLT)

DLTs are defined, in the presence of supportive care, as any Grade 3 or 4 toxicity that is possibly, probably, or definitely related to the study drug. The maximum tolerated dosage is defined as the dose level below that causing DLT in at least two patients. The length of the DLT window will be at least 28 days, and this time interval must elapse before completion of one cohort and initiation of the next.

Non-hematologic toxicities such as rash, nausea, vomiting and hypertension will only be considered DLTs if they remain grade 3 or greater despite maximal medical therapy 72 hours after maximal medical therapy is initiated. The first deep venous thrombosis or pulmonary embolism will not be considered a DLT because these complications are common among patients with high-grade gliomas. Patients who develop DVT and/or PE may receive anticoagulation therapy and resume the clinical trial once clinically stable. A second DVT or PE on optimal medical therapy will be considered a DLT.

| **Number of Patients with DLT**  **At a Given Dose Level** | **Escalation Decision Rule** |
| --- | --- |
| 0 out of 3 | Enter 3 patients at the next dose level |
| > 2 | Dose escalation will be stopped. This dose level will be declared the maximally administered dose (highest dose administered). Three (3) additional patients will be entered at the next lowest dose level if only 3 patients were treated previously at that dose. |
| 1 out of 3 | Enter at least 3 more patients at this dose level.   - If 0 of these 3 patients experience DLT, proceed to the next dose level. - If 1 or more of this group suffer DLT, then dose escalation is stopped, and this dose is declared the maximally administered dose. Three (3) additional patients will be entered at the next lowest dose level if only 3 patients were treated previously at that dose. |
| <1 out of 6 at highest dose level below the maximally administered dose | This is generally the recommended phase 2 dose. At least 6 patients must be entered at the recommended phase 2 dose. |

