The table above describes the dose escalation algorithm. If a DLT is encountered in 1 patient at a given dose level/cohort, an additional 3 patients will be enrolled at that dose level. If 2 patients in any cohort experience a DLT than the next lower dose level will be considered the MTD and no further dosage escalation will be performed. Three additional patients will be treated at the next lowest dose level if only 3 patients were previously treated at that level. If 3 patients are treated at the maximum dose without experiencing a DLT, an additional 3 patients will be treated at that dose level. At least 6 patients must be treated at the MTD. At least 28 days must elapse between the completion of one cohort to the beginning of the next cohort.

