## 6.7 - Data Saftey Monitoring Plan

The data and safety monitoring plan will involve the continuous evaluation of safety, data quality and data timeliness. Investigators will conduct continuous review of data and patient safety at their regular Disease Group meetings (at least monthly) and the discussion will be documented in the minutes. The PI of the trial will review toxicities and responses of the trial where applicable at these disease center meetings and determine if the risk/benefit ratio of the trial changes. Frequency and severity of adverse events will be reviewed by the PI and compared to what is known about the agent/device from other sources; including published literature, scientific meetings and discussions with the sponsors, to determine if the trial should be terminated before completion. Serious adverse events and responses will also be reviewed by the OSUCCC Data and Safety Monitoring Committee (DSMC). The PI will also submit a quarterly progress that will be reviewed by the committee per the DSMC plan. All reportable Serious Adverse Events (SAE) will also be reported to the IRB of record as per the policies of the IRB.

|  | Within 4 weeks prior to catheter Placement | Day of surgery, catheter placement, and infusion | Day after surgery | Post-infusion day 1 | Day 7 | Day 14 | Day 28 | Week 8 | Week 12 | Week 16 | Week 22 | Week 30 |
| --- | --- | --- | --- | --- | --- | --- | --- | --- | --- | --- | --- | --- |
| Informed Consent | X |  |  |  |  |  |  |  |  |  |  |  |
| Inclusion/Exclusion  Criteria | X |  |  |  |  |  |  |  |  |  |  |  |
| Pathology | X | X |  |  |  |  |  |  |  |  |  |  |
| Medical History | X |  |  | X |  |  | X | X | X | X | X | X |
| Concomitant Meds | X | X |  | X |  |  | X | X | X | X | X | X |
| Physical Exam and Vital Signs | X | X | X | X |  | X | X | X | X | X | X | X |
| Neurological examination | X | X | X | X |  | X | X | X | X | X | X | X |
| MMSE | X | X | X | X |  | X | X | X | X | X | X | X |
| Performance Status Determination | X | X | X | X |  | X | X | X | X | X | X | X |
| CBC with differential and platelets, | X | X | X | X | X | X | X | X | X | X |  |  |
| Comprehensive Metabolic Profile | X | X | X | X | X | X | X | X | X | X |  |  |
| Pregnancy Testing | X |  |  |  |  |  |  |  |  |  |  |  |
| MRI Brain^1^ | X |  |  |  |  |  |  | X |  | X |  | X |
| AE monitoring | X | X | X | X | X | X | X | X | X | X | X | X |
| CT Brain |  | X |  |  |  |  |  |  |  |  |  |  |

7 – Study Calendar

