# 9 - Statistical Considerations

A standard phase I study design utilizing dose escalation as defined in section 2.0 will be used. A maximum of 42 patients will be accrued. Descriptive statistics of response/efficacy and tolerance of treatments will be used. Only patients who received study drug will be considered for endpoint analysis. Patients that did not receive study treatment (catheter placement and convection enhance delivery of carboplatin) will be replaced at the current dose cohort.

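### After the first patient the 28-day DLT window has no stated start, and Section 9 does not replace treated patients who are part-dosed or lost before it ends

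*Protocol*

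**What the plan says.** - Section 5.2, first patient only: "This first patient will be observed for 28 days after completion of the infusion, prior to enrollment of additional patients".
- Sections 5.2 and 5.13, all patients: "The length of the DLT window will be at least 28 days, and this time interval must elapse before completion of one cohort" and the start of the next. No day zero is given.
- Section 5.12: "At least 28 days must elapse between completing enrollment in a cohort level and beginning treatment at the next cohort level".
- Section 5.13, text after the table: "At least 28 days must elapse between the completion of one cohort to the beginning of the next cohort". Completion of a cohort is not defined.
- Section 5.9: "Infusions will start preferably on postoperative day 1, but could be delayed up to postoperative day 7". The infusion lasts 72 hours.
- Section 7, study calendar: the columns run "Post-infusion day 1 | Day 7 | Day 14 | Day 28". The origin of Day 28 is not stated.
- Section 9: "Only patients who received study drug will be considered for endpoint analysis". Also: "Patients that did not receive study treatment (catheter placement and convection enhance delivery of carboplatin) will be replaced at the current dose cohort". Neither sentence sets a minimum infused dose or a minimum follow-up.

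**The concern.** The DLT count over this window is the only thing that opens the next dose level, and it also fixes the MTD. Two gaps affect the same 0/3 or 5/6 count.

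**Timing.** The rule that is precise about infusion covers one patient. The Section 5.12 rule that covers every later cohort counts from enrolment, which precedes surgery and infusion. Two teams could apply the same protocol and give the last patient of a cohort different lengths of observation before escalating.

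**Evaluability.** A treated patient may stop the infusion on request, die of tumour, or be lost before 28 days without a DLT. Section 9 keeps that patient in the analysis and does not provide a replacement. The patient can then count as one of three, or one of five in six, without DLT, although the dose or the observation was incomplete. A patient who stops the infusion is still followed, so that patient is under-dosed rather than lost.

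**Working it through.** **Timing**

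Inputs: volume 54 mL and rate 0.75 mL/hr (Section 5.12.1); infusion start on postoperative day s = 1 to 7 (Section 5.9); 28-day clock (Sections 5.2, 5.12, 5.13).

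1. The plan's own figure reproduces: 54 / 0.75 = 72 hours = 3 days.
2. Infusion therefore ends on postoperative day s + 3, that is day 4 to day 10.
3. Days observed after infusion ends, when the clock expires = clock start + 28 − (s + 3), counted from surgery.

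| Clock starts at | Days after infusion end (s = 1 / s = 7) | Short of first-patient rule |
| --- | --- | --- |
| Surgery, or enrolment on the day of surgery | 24 / 18 | 4 / 10 |
| Start of infusion | 25 / 25 | 3 / 3 |
| End of infusion | 28 / 28 | 0 / 0 |

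On the first-patient rule the gate opens 28 days after day 4 to 10, so on day 32 to 38 after surgery. Under the Section 5.12 clock, each day between enrolment and surgery removes one further day. The protocol does not fix that interval.

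Size in the 3+3 rule, as an illustration only. Assume a true DLT rate of 33%, onset uniform over 28 days after infusion, and only the last patient of each group of three cut short. P(escalate) = P(0/3) + P(1/3) × P(0/3). With full observation this is 0.434. With 25 days for the last patient it is 0.457, with 24 days 0.465, and with 18 days 0.511.

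**Evaluability**

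Let p be the true DLT rate and f the share of the lost patient's DLT risk already observed. Both are assumptions.

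Given that one of three treated patients is lost, P(apparent 0/3) = (1 − p)² (1 − f p):

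| | p = 0.2 | p = 0.3 | p = 0.4 |
| --- | --- | --- | --- |
| f = 1 (nothing lost) | 0.512 | 0.343 | 0.216 |
| f = 0.5 | 0.576 | 0.417 | 0.288 |
| f = 0 (outer bound) | 0.640 | 0.490 | 0.360 |

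For the six-patient count, P(at most 1 DLT in 6) = 0.655, 0.420, 0.233. If one of the six gives no information, it becomes P(at most 1 in 5) = 0.737, 0.528, 0.337.

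Those figures are conditional on a loss. Averaged over an assumed loss probability q per patient, P(apparent 0/3) = [(1 − q)(1 − p) + q(1 − f p)]³:

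| | p = 0.2 | p = 0.3 | p = 0.4 |
| --- | --- | --- | --- |
| q = 0.02, f = 0.5 | 0.516 | 0.347 | 0.220 |
| q = 0.02, f = 0 | 0.520 | 0.352 | 0.225 |
| q = 0.10, f = 0.5 | 0.531 | 0.366 | 0.238 |
| q = 0.10, f = 0 | 0.551 | 0.389 | 0.262 |

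Against the f = 1 row above, the rise runs from about 0.004 (0.516 − 0.512) to about 0.046 (0.389 − 0.343), or roughly 0.4 to 5 percentage points.

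The range for q is not in the protocol. As a rough check, the 9-month median survival quoted in Section 2.3 for intravenous carboplatin, with constant hazard, gives death within 31 days (3 days of infusion plus 28) of 1 − 2^(−31/274) = 0.075. Eligibility requires a life expectancy of at least 3 months and a Karnofsky status of at least 60 (Section 4.2), which should lower this.

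**The case against.** The case against is substantial, and part of it stands.

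- The waits are all minimums and apply together. Meeting Section 5.12 does not waive the requirement in Sections 5.2 and 5.13 that the DLT window elapse. A DLT there is a toxicity related to the study drug, so its window is most naturally read as starting with exposure. On that reading the shortfall is 3 days or none. This stands.
- The calendar leans the same way. With a day-7 start, infusion ends on day 10 and the first post-infusion day falls on about day 11 after surgery, later than a Day 7 counted from surgery. The column order holds for every permitted schedule only on an infusion-based count. But one column puts surgery and infusion on a single day, so this supports the reading without settling it.
- A reader might infer that the next cohort could be treated before the last infusion has finished, because calendar screening may precede catheter placement by up to 4 weeks. The documents do not support this: the enrolment date is not defined, and Section 5.13 would still block it.
- An evaluable set is often left to the SAP. However, Section 9 itself states the analysis and replacement rules, and escalation is decided during conduct; a later analysis set cannot undo it.
- Under-dosing is narrow. Of the stopping reasons in Section 5.14, drug-related grade 3 or 4 toxicity is itself a DLT, and Section 8.1 makes grade 2 intracranial haemorrhage one too. That leaves patient request, during a monitored 72-hour inpatient infusion. Death from tumour and loss to follow-up remain as separate routes.
- A stricter rule for a first patient can be deliberate. If so, the protocol should still state the start that applies to everyone else.

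**Conclusion.** The point holds as a gap in the stated rules. It is not a contradiction, and it does not show that escalation will rest on short observation. After the first patient, day zero is missing, and Section 5.12 counts from an event before drug exposure. The shortfall against the first-patient rule is 3 days if the window starts with infusion and 0 if it starts at the end of infusion. It reaches 4 to 10 days only if a team uses the Section 5.12 clock with surgery on the enrolment day, or counts Day 28 from surgery.

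The Section 9 gap rests on its stated replacement rule. A reader might take the change from 0.51 to 0.64, or from 0.34 to 0.49, as the general inflation of an apparent 0/3. It is not: those are outer bounds that assume one of three patients has been lost and contributes no DLT information. The average effect is about 0.4 to 5 percentage points, assuming 2 to 10% loss per patient and DLT rates of 20 to 40%.

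This should be fixed because the rules govern each dose step in a phase I brain-infusion trial and the correction is cheap. Confidence is medium, since the timing effect depends on which clock a team uses.

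**What to change.** - **Sections 5.2, 5.12 and 5.13, including the text after the table:** state that each patient's DLT window runs from the start of infusion to 28 days after its end. State that the next level may be treated only when every patient in the cohort has completed the window or had a DLT.
- **Section 7:** count Day 28 from the end of infusion.
- **Section 9:** define DLT-evaluable as having had a DLT, or having received the planned infusion and completed the window. Replace treated patients who are not evaluable for escalation and MTD decisions, and keep them in the safety tables.

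This is a cheap improvement: a wording amendment with no new visits. It costs 4 to 10 days per cohort against the Section 5.12 clock with no enrolment-to-surgery lag, 3 days against a window from infusion start, and nothing against a window from infusion end. It also costs an occasional replacement patient within the 42-patient maximum.

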### 5.12.1 - Dose escalation schedule

The Dose Escalation Schedule is indicated in the following table. Carboplatin will be administered in a volume of 54 mL at a flow rate of 0.75 mL/hr over 72 hrs.

| Dose Escalation Schedule | |
| --- | --- |
| Dose Level | Carboplatin Dosage |
| Level 0 | 1 µg |
| Level 1 | 2 µg |
| Level 2 | 4 µg |
| Level 3 | 8 µg |
| Level 4 | 16 µg |
| Level 5 | 32 µg |
| Level 6 | 64 µg |
| Level 7 | 85 µg |
| Level 8 | 107 µg |
| Level 9 | 128 µg |

### 5.12.2 – Dose escalation Justification

Justification for these doses is as follows:

In rats, we routinely have administered carboplatin by CED over 30 min to one cerebral hemisphere (600 mg), and this was well tolerated. The rat brain weighs ~1.2 g or 600 mg per cerebral hemisphere. The volume administered was 10 µL containing 20 µg of carboplatin, which was equivalent to 2 µg of carboplatin per 60 mg of rat brain. This was equivalent to 0.033 µg of carboplatin in 0.0165 µL/mg brain or 33 µg in 16.5 µL/g brain. The human brain is 1000 times larger at 1.2 kg total and 600 g per hemisphere. If we scale up the rat dose to an adult human brain, this would be equivalent to 19.9 mg in 9.9 mL per cerebral hemisphere (33 µg/gm wt brain x 600=19,800 µg in 9900 µL=19.8 mg of carboplatin in 9.9 mL), which is 156X higher than the highest dose of carboplatin that we propose to administer (128 µg in 54 mL). The relative volume being infused as a function of time is much less. For the rat, 10 µL was infused into a 600 mg hemisphere over 0.5 hours resulting in a flow rate of 33 µL/g/hour. In our proposal, 54 ml infused into a 600 g hemisphere over 72 hours yields a flow rate of 1.25 µL/g/hour. Furthermore, the concentration of carboplatin in the rat experiments was 2 mg/ml, whereas the highest concentration of carboplatin in our proposal is 2.37 µg/ml.

In Strege, Jallo and Guarnieri’s report[[43](#_ENREF_43)], they stated that the MTD of carboplatin delivered to the brain stem of a 200 g Fischer rat by Alzet pumps at a flow rate of 1 µL/h over 7 days was 100 µg. They used a conversion factor of 0.5 to estimate the MTD to a 3 kg monkey, which was estimated to be 0.25 mg/kg (3 mg/m^2^) of carboplatin. Based on this, doses of carboplatin were diluted to be delivered over more than 30 days, and were delivered at 0.42 µL/h. Two animals received 0.1 x eMTD (0.025 mg/kg); three received 0.3 x eMTD (0.075 mg/kg); five received 1 x eMTD (0.25 mg/kg); and three received 3 x eMTD (0.75 mg/kg.)

Permission was requested and received (please see letter in the Appendix) to reference IND #71,156 submitted by [name] from Johns Hopkins University. This proposed IND contains toxicity data on the administration of carboplatin by CED to the brainstem of primates, as well as safety data regarding the use of catheters implanted into neural tissue. This proposed protocol was designed to treat a pediatric population with brainstem tumors and the dosing regimen that was recommended to them by the FDA was based on this. Tables 2 and 3 provide further references used for selecting the total dose of carboplatin as well as the variables chosen for infusion.

Based on these considerations, we believe that the Dosing Escalation Schedule indicated in the above table represents a safe starting point. If it turns out that the 128 µg dose is well tolerated, then permission from the FDA will be obtained to further escalate the dose of carboplatin until toxicity has been demonstrated.

## 5.13 - Dose-Limiting Toxicity (DLT)

DLTs are defined, in the presence of supportive care, as any Grade 3 or 4 toxicity that is possibly, probably, or definitely related to the study drug. The maximum tolerated dosage is defined as the dose level below that causing DLT in at least two patients. The length of the DLT window will be at least 28 days, and this time interval must elapse before completion of one cohort and initiation of the next.

Non-hematologic toxicities such as rash, nausea, vomiting and hypertension will only be considered DLTs if they remain grade 3 or greater despite maximal medical therapy 72 hours after maximal medical therapy is initiated. The first deep venous thrombosis or pulmonary embolism will not be considered a DLT because these complications are common among patients with high-grade gliomas. Patients who develop DVT and/or PE may receive anticoagulation therapy and resume the clinical trial once clinically stable. A second DVT or PE on optimal medical therapy will be considered a DLT.

| **Number of Patients with DLT**  **At a Given Dose Level** | **Escalation Decision Rule** |
| --- | --- |
| 0 out of 3 | Enter 3 patients at the next dose level |
| > 2 | Dose escalation will be stopped. This dose level will be declared the maximally administered dose (highest dose administered). Three (3) additional patients will be entered at the next lowest dose level if only 3 patients were treated previously at that dose. |
| 1 out of 3 | Enter at least 3 more patients at this dose level.   - If 0 of these 3 patients experience DLT, proceed to the next dose level. - If 1 or more of this group suffer DLT, then dose escalation is stopped, and this dose is declared the maximally administered dose. Three (3) additional patients will be entered at the next lowest dose level if only 3 patients were treated previously at that dose. |
| <1 out of 6 at highest dose level below the maximally administered dose | This is generally the recommended phase 2 dose. At least 6 patients must be entered at the recommended phase 2 dose. |

The table above describes the dose escalation algorithm. If a DLT is encountered in 1 patient at a given dose level/cohort, an additional 3 patients will be enrolled at that dose level. If 2 patients in any cohort experience a DLT than the next lower dose level will be considered the MTD and no further dosage escalation will be performed. Three additional patients will be treated at the next lowest dose level if only 3 patients were previously treated at that level. If 3 patients are treated at the maximum dose without experiencing a DLT, an additional 3 patients will be treated at that dose level. At least 6 patients must be treated at the MTD. At least 28 days must elapse between the completion of one cohort to the beginning of the next cohort.

